# Efficacy of a video‐viewing intervention of smartphone‐based positive word stimulation on depressive symptoms in individuals with subthreshold depression: Protocol for a randomized controlled trial

**DOI:** 10.1002/pcn5.70284

**Published:** 2026-01-31

**Keywords:** depression, mental health, MHealth, smartphone, subthreshold depression

## Abstract

**Background:**

Interventions targeting subthreshold depression (StD) are critically important for preventing major depressive disorder's onset. Our smartphone‐based, video‐viewing website (SPSRS), which presents positive word stimulation in videos, is a novel intervention for improving StD's depressive symptoms. Because no rigorous evidence exists for SPSRS's efficacy, this trial aims to evaluate the SPSRS intervention's efficacy on depressive symptoms.

**Methods:**

The trial will be an evaluator‐blinded, randomized, 5‐week, parallel‐group superiority trial designed to assess whether the SPSRS intervention (experimental group) is effective compared to no intervention (waiting‐list control group). In a 1:1 ratio, 400 participants with StD will be randomly assigned to an experimental group (*n* = 200) or a waiting‐list control group (*n* = 200). The experimental group will receive a 10‐min SPSRS video‐viewing intervention once daily for 5 weeks; when the intervention ends, the waiting‐list control group will receive the treatment upon request. The intervention's primary outcome will be the mean change from baseline on the Center for Epidemiologic Studies Depression Scale; secondary outcomes will include the mean change from baseline on the Kessler Psychological Distress Scale and the Generalized Anxiety Disorder seven‐item scale.

**Result:**

The results are presented according to the protocol.

**Discussion:**

This trial's confirmation of SPSRS's efficacy could lead to new StD intervention strategies and provide interventions tailored to patient needs.

## INTRODUCTION

Over the past few decades, the clinical significance of subthreshold depression (StD) (e.g., subsyndromal, subclinical, or minor depression) has received considerable attention.^1^, ^2^ StD does not meet diagnostic criteria for major depressive disorder (MDD) but is considered present when an individual experiences clinically significant depressive symptoms measured by patient‐reported outcomes (PROs).^3^ StD occurs across all age groups, and a systematic review indicated its prevalence at 11.02%.^2^, ^4^ Moreover, StD causes such problems as diminished daily functioning, reduced quality of life, worsening health status, increased economic costs, and increased mortality.^3^, ^5^, ^6^, ^7^, ^8^, ^9^, ^10^ But particularly important is that studies have indicated that StD exists on the spectrum of MDD and that individuals with StD are more likely to transition to MDD.^1^, ^2^, ^6^ Therefore, StD interventions' development and implementation are essential not only for improving various problems caused by StD but also for preventing the onset of MDD, a major public health issue.

Systematic reviews have demonstrated that psychotherapy improves depressive symptoms in individuals with StD and thus may reduce the risk of MDD onset.^11^, ^12^ Therefore, investigating psychotherapy's therapeutic efficacy further and promoting its usage is important. However, developing and investigating various other treatment options is necessary because studies have suggested that considering patients' treatment preferences and approaches is necessary to motivate treatment adherence, prevent treatment dropout, and lead to more efficacious mental‐health outcomes.^13^, ^14^, ^15^ Given patient preferences' influence on treatment's efficacy, developing a variety of treatment strategies to reduce StD's depressive symptoms is crucial.

Our newly developed, smartphone‐based video‐viewing website (SPSRS) can serve as such an intervention strategy.^16^ Designed based on word stimulation research and positive words from a qualitative study of patients with StD, SPSRS displays two words of stimulation to improve depressive symptoms and prevent progression to MDD.^17^, ^18^, ^19^, ^20^ The SPSRS website has the advantage of free use on ever‐more‐ubiquitous smartphones, thereby reaching many who can benefit from treatment.^21^, ^22^, ^23^ Significantly, SPSRS uses the YouTube application programming interface (API), enabling users to watch videos uploaded to YouTube directly via SPSRS. Thus, people with StD can choose preferred, relevant videos and have fun working toward improving their depressive symptoms.

To date, several studies have demonstrated SPSRS's efficacy.^24^, ^25^, ^26^, ^27^, ^28^, ^29^ First, a study investigating its feasibility found it safe and easy to use, with no adverse events (AEs) during intervention.^16^ After a 5‐week intervention, a pilot randomized controlled trial (RCT) showed moderate improvement in the experimental group's depressive symptoms (measured by the Center for Epidemiologic Studies Depression Scale [CES‐D, Japanese version]) compared to those of the waiting‐list control group.^25^, ^27^ This pilot's unique strength lies in its ability to improve StD depressive symptoms using CES‐D scores.

Of various PROs identifying individuals with StD and assessing changes in depressive symptoms, the widely used CES‐D effectively evaluates StD.^2^, ^30^ Importantly, the CES‐D score offers advantages over other PROs (e.g., the Beck Depression Inventory‐II [BDI‐II], the Patient Health Questionnaire‐9 [PHQ‐9]) when evaluating SPSRS's intervention efficacy on StD depressive symptoms. The CES‐D score includes four factors: (1) somatic and retarded activity, (2) depressed affect, (3) positive affect, and (4) interpersonal problems.^31^ Specifically, when measuring depressive symptoms, other PROs (e.g., BDI‐II, PHQ‐9) do not include positive affect, but the CES‐D's total score indicates symptoms' severity based on whether a person has experienced a depressive episode and whether they feel happy, making it possible to measure depressive symptoms' various aspects in detail.^31^, ^32^, ^33^ Especially because SPSRS uses positive words to improve depressive symptoms, the CES‐D containing positive items is likely the most suitable PRO for accurately measuring SPSRS's intervention efficacy. Therefore, the previously conducted pilot RCT appropriately evaluated SPSRS's efficacy with the patients with StD population.

Notably, no formal sample size calculation was performed for the previous pilot RCT; however, it was conducted with the minimum sample size to ensure the results' scientific validity (16 participants per group, 32 participants total).^25^ Even so, data from small samples inherently contain inaccuracies.^34^, ^35^, ^36^ Therefore, to determine SPSRS's intervention efficacy, the pilot's changes in CES‐D scores are preliminary, emphasizing the need for a full‐scale RCT based on a formal sample size.

### Primary hypothesis and objectives

To that end, we have planned an RCT with the primary objective of verifying SPSRS's efficacy for individuals with StD. We hypothesize that the SPSRS intervention (experimental group) will be effective in reducing depressive symptoms, as assessed by the CES‐D, in individuals with StD compared to no intervention (waiting‐list control group).

### Identifying optimal intervention timing to enhance SPSRS intervention's efficacy

If SPSRS proves efficacious in reducing StD's depressive symptoms, estimating its appropriate intervention duration is crucial, especially because its video‐viewing time has not yet been sufficiently established. Identification of appropriate intervention duration not only enables theoretical refinement of the therapeutic mechanism and SPSRS process but can also help clarify its clinical implementation. Therefore, the trial's secondary objective is to explore an appropriate intervention duration.

## METHODS AND ANALYSIS

### Trial design

This trial is a 5‐week, evaluator‐blinded, 1:1 parallel‐group superiority RCT to determine SPSRS efficacy. It was designed in accordance with the Recommendations for Interventional Trials (SPIRIT) 2025 statement and SPIRIT‐PRO.^37^, ^38^

### Eligibility

Participants will be selected according to the following.

#### Inclusion criteria

(1)Male or female.(2)18–64 years old.(3)CES‐D score of 16 or higher.^31^, ^39^
(4)Own a smartphone.(5)Have provided electronic informed consent before participation.

#### Exclusion criteria

(1)Individuals with a lifetime history of mental illness.(2)Individuals receiving treatment from mental‐health professionals.(3)Persons with visual or hearing impairments that adversely affect their daily lives.(4)PHQ‐9 Item 1 (Little interest or pleasure in doing things) or Item 2 (Feeling down, depressed, or hopeless) with responses of “several days,” “more than half the days,” or “nearly every day,” and who also responded “more than half the days” or “nearly every day” to five of nine items.^39^

Generally, StD does not meet diagnostic criteria for MDD but is considered present when an individual experiences clinically significant depressive symptoms as measured by PRO.^3^ However, because a market research company will conduct this trial, ruling out MDD based on structured interviews such as the Mini‐International Neuropsychiatric Interview (MIINI) will be difficult.^40^ In such cases, one approach is to use the PRO Depression Scale to rule out MDD.^39^, ^41^, ^42^, ^43^, ^44^, ^45^ In a previous study, individuals were judged to have MDD if, in addition to having a CES‐D score of 16 or higher, they responded “several days,” “more than half the days,” or “nearly every day” to PHQ‐9 Item 1 (Little interest or pleasure in doing things) or Item 2 (Feeling down, depressed, or hopeless), and responded “more than half the days” or “nearly every day” to five or more of the nine items.^39^ In contrast, those with a CES‐D score of 16 or higher who did not meet the PHQ‐9 criteria for MDD were judged to have StD.^39^ In this trial, StD is defined according to the identification method used in the previous study.

### Study setting and recruitment timeline

This trial will recruit participants from the panel network (36 million members) of a Japanese market research company (Macromill Group, Tokyo) from October 1, 2025, to March 31, 2030. The research firm will email invitations to panelists aged 18–64, explaining the trial's purpose and procedures. The invitation will include an electronic consent option; individuals who check “consent” will be deemed to have agreed to participate in the main trial and can proceed to the online questionnaire for eligibility assessment. Participants who meet eligibility criteria will then undergo a baseline assessment and be considered enrolled. By the Central Registration Center at Kagoshima University, they will subsequently be randomly assigned to the experimental or the waiting‐list control group. Participants will be scheduled to complete Japanese versions of the CES‐D, Kessler Screening Scale for Psychological Distress (K‐6), and Generalized Anxiety Disorder‐7 (GAD‐7) questionnaires at 3 and 5 weeks after the intervention begins.^31^, ^46^, ^47^, ^48^, ^49^ Additionally, at 5 weeks after the intervention begins, the Global Rating of Change (GRC) scales will be assessed in addition to the CES‐D, K6, and GAD‐7.^50^, ^51^ The CES‐D will be administered during the main trial's eligibility assessment, while the K6 and GAD‐7 will be administered during baseline assessment. At 3 weeks after the intervention begins, assessments will be conducted in the following order: CES‐D, K6, and GAD‐7. At 5 weeks, assessments will be conducted in the following order: CES‐D, K6, GAD‐7, and GRC scales. Demographic information and lifestyle characteristics will be assessed only at baseline. Figure 1 shows the study's flowchart, and Table 1 shows the assessment schedule.

**Figure 1 pcn570284-fig-0001:**
[figure not shown]
CONSORT flowchart of study design.

**Table 1 pcn570284-tbl-0001:** Assessment schedule.

[figure not shown]

Abbreviations: CES‐D, center for epidemiologic studies depression scale; GAD‐7, generalized anxiety disorder‐7; GRC, global rating of change; K‐6, kessler screening scale for psychological distress.

### Interventions

#### Experimental group

The experimental group will receive a video‐viewing intervention using SPSRS, which allows participants to search for videos by keyword and watch them (similar to YouTube).^16^ To enable participants to access YouTube videos, SPSRS utilizes the YouTube API. Thus, to leverage SPSRS's benefits, participants will choose which videos to watch and enjoy.

The key difference between SPSRS and video‐viewing sites like YouTube is that SPSRS presents two types of word stimulation during the video. First, a confidence‐boosting word or phrase randomly appears (17 ms) in one of the screen's four corners: *can*, *let us try*, *good luck*, *able*, or *do not worry*.^17^ Immediately afterward, a positive word appears (150 ms) at the screen's center: *nice*, *great*, *fantastic*, *satisfactory*, or *enjoyable*.^18^ These words repeat every 5 s. The experimental group will engage in SPSRS video‐viewing for at least 10 min per day (at least 70 min per week; at least 350 min over 5 weeks), determined based on the previous pilot RCT.^25^

This trial will undoubtedly enroll participants with diverse preferences in video content, and each individual is free to select videos that interest them so that the intervention is applicable to a wide adult demographic. However, as the SPSRS utilizes videos from YouTube, participants will not have access to videos that violate YouTube's Community Guidelines (e.g., due to violent, sexual, or fraudulent content). Additionally, participants may pause or stop the video at any time if they experience discomfort or health effects while watching. While the SPSRS system does not currently have its own reporting function, users can directly navigate from the SPSRS video playback screen to YouTube and report violations.

Participants will receive the SPSRS link and instructions for its use via email. To increase adherence, a templated text reminder will be sent once a week.^25^, ^52^ Additionally, SPSRS not only displays the daily required viewing time on the home screen but also allows participants to check their current viewing time via the history function.

#### Waiting‐list control group

The waiting‐list control group will not receive instructions to implement the video‐viewing intervention using SPSRS or other websites (such as YouTube) during the 5‐week intervention period. However, if participants wish to use the SPSRS, they will receive the video‐viewing intervention using the SPSRS after completing a questionnaire 5 weeks after the intervention begins.

#### Relevant concomitant care and interventions permitted/prohibited during the trial

From an ethical standpoint, no restrictions on interventions will be imposed in this trial.

#### Criteria for discontinuing or modifying allocated interventions

(1)A participant wishes to discontinue the intervention, and continuing the intervention is determined to be difficult.(2)The entire clinical trial is discontinued.(3)A participant becomes ineligible after enrollment.(4)The research team determines that discontinuing the intervention is warranted.

Participants are not considered to have withdrawn from the trial when the intervention ends and are requested to undergo primary and secondary outcome assessments. Participants who refuse to undergo assessment or withdraw consent are considered to have withdrawn. Participants will be excluded from the intention‐to‐treat (ITT) analysis only if they are deemed unable to meet eligibility criteria.

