### Outcomes

This trial's primary outcome will be the mean change in the CES‐D's total score from baseline to the intervention's scheduled end (5 weeks).^31^ The secondary outcomes are mean changes in total scores of the K6 and the GAD‐7 from baseline to the intervention's end (5 weeks).^46^, ^47^, ^48^, ^49^

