#### Analysis of primary and secondary outcomes

Data analysis will be based on ITT analysis. Therefore, participants will be analyzed based on their initial group assignment regardless of adherence to the intervention. Assuming primary outcome data are randomly missing, the trial will use a linear mixed model (LMM) with restricted maximum‐likelihood estimation to compare mean changes between the experimental and waiting‐list control groups from baseline to Week 5.^72^ LMM can address defects arising in clinical trials and use all available data to estimate results, thereby making it possible to compare the experimental group that addressed the missing data to the waiting‐list control group.^72^

The CES‐D score is the dependent variable; the independent variables are group (experimental or control), time (baseline, 3 weeks, 5 weeks), and interaction between group and time—all treated as fixed‐effect factors, with participants treated as random‐effect factors. Baseline CES‐D scores will be included as covariates in the LMM. Additionally, to confirm results' robustness for the primary outcome, sensitivity analyses will be conducted using multiple imputation methods and per‐protocol analyses only for participants who provided complete data.^73^ Statistical significance will be set at *p* < 0.05 using a two‐tailed test. Additionally, Hedge's *g* will be calculated as the effect size between the two groups.^74^, ^75^ Secondary outcomes will be analyzed using the same procedures as primary outcomes; however, due to secondary outcomes' exploratory nature, no adjustments for multiple comparisons will be performed. No subgroup analyses are currently planned. LMM calculations will use the lmerTest package, and Hedge's *g*‐statistic will be calculated using the compute.es package. Multiple comparisons will be performed using the mice package.

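### The ITT exclusion for ineligibility is not limited to status before randomisation, so read literally it permits participants to be dropped for reasons tied to their outcome

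*Protocol article*

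**What the plan says.** Four parts of the protocol article bear on this.

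- **Criteria for discontinuing or modifying allocated interventions.** Item (3) on the list is "A participant becomes ineligible after enrollment". The text below the list says "Participants are not considered to have withdrawn from the trial when the intervention ends" and that their primary and secondary outcomes are still requested. It then permits exclusion from the ITT "analysis only if they are deemed unable to meet eligibility criteria". No time point is attached to that test, and nothing says who applies it or what that person knows.
- **Inclusion and exclusion criteria.** Entry requires a "CES‐D score of 16 or higher". Exclusions include a lifetime history of mental illness and "Individuals receiving treatment from mental‐health professionals".
- **Relevant concomitant care.** During the trial "no restrictions on interventions will be imposed in this trial", so mental-health treatment may begin after randomisation.
- **Outcomes and analysis.** The "primary outcome will be the mean change in the CES‐D's total score from baseline" to week 5, and the CES-D is completed again at weeks 3 and 5. The analysis section says "participants will be analyzed based on their initial group assignment regardless of adherence to the intervention". It neither repeats nor limits the eligibility exclusion.

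**The concern.** An ITT comparison is protected by randomisation as long as membership of the analysis set does not depend on anything that happens after allocation. Here the test for membership is eligibility, and eligibility has no fixed reference time. One criterion is a cut-off on the primary outcome scale. Two others, mental illness and mental-health treatment, are events that deterioration can bring about.

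If the exclusion reached people who became ineligible later, the primary analysis could lose participants because of how they fared. Participants and therapists are not blinded, so the events that make someone ineligible, such as seeking care or reporting a deterioration, could also occur or come to light at different rates in the two arms. The rule governs who enters the confirmatory analysis, and it cannot be settled credibly once outcomes have been seen.

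**Working it through.** **1. The plan's own figure.** The documents quantify nothing on this point, but the sample size is the natural benchmark. With g = 0.4, two-sided alpha 5% and power 80% (Sample size section), the normal formula gives 2 × (1.960 + 0.842)² / 0.4² = 98.1, so 99 per group. The t-test version gives 99.08, rounded up to 100. Allowing 50% dropout, 100 / (1 − 0.5) = 200 per group and 400 in total. The stated size reproduces.

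**2. Which criteria can change after randomisation.**

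| Criterion | Can it change? | How it would come to light |
|---|---|---|
| CES-D of 16 or more | Yes, downward through improvement | Scheduled at weeks 3 and 5 |
| No mental illness | Yes, new onset | No scheduled question described; contact with the team or adverse event reports |
| No mental-health treatment | Yes, concomitant care is unrestricted | As above |
| PHQ-9 rule for MDD | In principle | Not a scheduled route: the PHQ-9 is not listed at week 3 or 5 |

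The routes point in opposite directions. Falling below 16 identifies improvers. New illness or new treatment tends to identify people who have worsened.

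**3. Removing improvers (CES-D below 16).** The documents give no CES-D mean or SD, so these are assumed. Three settings were simulated: normal baseline with mean and SD of 22 and 7, 25 and 8, or 20 and 8 before truncation at 16; correlation 0.5 with week 5; an average improvement of 1 point besides regression to the mean; a baseline-adjusted estimate; and 100 evaluable per arm before exclusions. Power comes from a normal approximation.

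| Assumed mean, SD | Dropped, experimental / control | Estimate when truth is 0.4 | Power, all kept → after exclusion |
|---|---|---|---|
| 22, 7 | 30% / 17% | 0.24 | 87% → 54% |
| 25, 8 | 22% / 12% | 0.26 | 88% → 63% |
| 20, 8 | 39% / 25% | 0.21 | 86% → 44% |

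With no true effect, the same cut-off applied to both arms gave no bias and left the error rate at 5%.

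**4. Removing people who worsened, one arm only.** If the upper tail p of a standard normal outcome is removed from one arm, that arm's mean falls by φ(z₁₋ₚ)/(1 − p).

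- p = 3%: 0.070 SD.
- p = 5%: 0.1031/0.95 = 0.109 SD, which is 0.109/0.4 = 27% of the planned effect.
- p = 10%: 0.1755/0.90 = 0.195 SD, which is 49% of it.

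In the simulated settings, with baseline adjustment and no true effect, removing the worst 5% of the experimental arm only gave a spurious benefit of about 0.09 SD and a two-sided error rate of about 11%. Removing the worst 10% gave 0.16–0.17 SD and 25–27%. The shares, and the restriction to one arm, are assumptions.

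**5. Removing people who worsened, common cut in both arms.** No bias when there is no true effect. When the truth is 0.4, the estimate shrinks to about 0.34 (worst 5% overall) or 0.30 (worst 10%).

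**6. Loss of numbers alone.** Starting from 100 per group with 80% power, losing 5%, 10% or 20% of evaluable participants leaves t-test power of 78%, 76% or 71%. The larger risk is selection.

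**The case against.** The best reply is that the sentence was meant for people found never to have qualified. Screening is an online self-report questionnaire completed by panel members, so a misreported history or current treatment could surface later, and a rule for such cases has an obvious purpose. Item (3) sits on a list about the intervention, and the ITT sentence uses different words and is framed restrictively. The text between them keeps people who stop the intervention in follow-up. This stands in part: the entry-only reading is plausible, and the link between item (3) and the ITT exclusion is inferred from related wording and placement. But the entry-only limit is not written down, and the same section shows that its authors had later ineligibility in mind.

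A reader might be tempted by four stronger claims, which the documents do not support.

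- **That the analysis section is contradicted.** Its promise concerns adherence, and eligibility is a different matter. The exclusion is left unreconciled there, which is less than a contradiction.
- **That the decision is unblinded.** The article does not say who decides or with what knowledge.
- **That the PHQ-9 rule would remove people who progress to MDD.** No repeat PHQ-9 is scheduled.
- **That a bias of a quarter to a half of the planned effect in favour of SPSRS should be expected.** That figure needs exclusion in one arm only, at assumed shares. It also concerns the opposite tail from the one eligibility item that is re-measured, where the bias runs against SPSRS.

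Leaving fine detail of analysis sets to an unseen analysis plan is normal. Here, however, the article states the exclusion rule, and states it too broadly.

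**Conclusion.** The point holds as a defect of wording in a rule that matters. Read literally, the exclusion reaches participants whose ineligibility arises after randomisation and is related to their outcome. Confidence is moderate, because a harmless intention is plausible.

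The direction of bias is not fixed. Under the assumed CES-D distributions, dropping everyone below 16 at week 5 would cut a true effect of 0.4 by roughly a third to a half. Dropping the worst 5% of one arm would shift its mean by about 0.11 SD before baseline adjustment. Both figures illustrate what the wording permits and are not predictions: they rest on assumed distributions and shares, and dropping every improver is unlikely to be what the authors intend. Whichever reading was meant, the same short restriction removes the risk.

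**What to change.** Replace the ITT sentence with one of two rules:

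1. every randomised participant is analysed in the arm assigned, with no eligibility exclusion; or
2. exclusion is limited to participants shown, from their status before randomisation, not to have met a criterion, as judged by someone blind to arm and outcome.

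Under either rule, add that ineligibility arising after randomisation never removes a participant from the ITT set, and that such participants' outcomes are still collected and used. Carry the same wording into the analysis section so that the two places agree. How the intervention itself is handled when someone becomes ineligible is for the sponsor to decide and does not affect this change.

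The cost is a sentence or two in a protocol amendment. No further data or participants are needed, and the sample size stays at 200 per group.
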